## Methods

### Trial Design and Oversight

We will conduct a 12-month, health care provider–level, randomized, 2‑period crossover simulation trial to evaluate the feasibility, usability, and preliminary effectiveness of FibroX, an explainable AI decision support tool for detecting MASLD‑associated advanced liver fibrosis (≥F3) in adults with T2D. Because FibroX is not currently used in routine clinical care, this study evaluates the tool in a simulated clinical environment. Each clinician serves as their own control (FibroX-enabled care vs usual care), separated by a 1-week washout. Distinct, nonoverlapping simulation case sets will be used in each study period, such that clinicians will not evaluate the same cases across periods, reducing case-recall bias and minimizing carryover related to prior exposure. The study involves no patient enrollment and uses deidentified or synthetic cases. Oversight is by the principal investigator and study steering team; a formal Data Monitoring Committee is not required given the minimal risk.

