### Sample Size

At least 36 health care providers (32 cases/health care provider) yield 1150 to 1280 paired decisions. Under pilot assumptions (accuracy 0.60 usual care vs 0.75 FibroX), McNemar test provides >80% power to detect a 15-point improvement at α=.05 after accounting for health care provider–level clustering via a conservative design effect. Precision estimates for feasibility and usability metrics are expected to be narrow enough to inform a subsequent multicenter trial.

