### Statistical Analysis

All analyses will follow an intention-to-treat principle, including all health care provider decisions regardless of sequence assignment. The primary comparison of diagnostic accuracy between FibroX-enabled care and usual care will use paired analyses to account for the crossover design. Sensitivity and specificity for detecting MASLD-associated advanced fibrosis will be compared using McNemar test for paired proportions. Overall discrimination will be assessed by calculating the area under the receiver operating characteristic curve for each condition, and calibration will be evaluated through intercept, slope, and calibration plots to determine agreement between predicted probabilities and observed outcomes.

To account for clustering at the health care provider level and the crossover design, mixed-effects logistic regression models will be used, specifying health care provider as a random effect and study condition, study period, and sequence assignment as fixed effects. Sensitivity analyses will also assess whether diagnostic performance differs by sequence assignment or period, which may suggest residual carryover or learning effects. These models will also adjust for case-level covariates such as age, BMI, and HbA_1c_ to explore potential confounding and heterogeneity. Secondary analyses will include net reclassification improvement to quantify whether FibroX improves assignment of cases into clinically appropriate triage categories compared with usual care. Bootstrap resampling will be used to generate CIs for net reclassification improvement and calibration metrics, ensuring robust estimation under small-sample conditions.

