Feasibility outcomes, including recruitment and completion rates, will be summarized descriptively with proportions and 95% CIs. Usability and trust scores from the SUS and AI trust scale will be analyzed using paired *t* tests or Wilcoxon signed-rank tests, depending on distributional assumptions. Cognitive workload scores from NASA-TLX will be compared similarly. Subgroup analyses will explore whether diagnostic performance varies across diabetes-related characteristics such as HbA_1c_, BMI, and duration of diabetes, using interaction terms in mixed-effects models. Missing data are expected to be minimal; if more than 5% of survey data are missing, multiple imputation under a missing-at-random assumption will be applied, with sensitivity analyses conducted using complete-case data. All statistical tests will be 2-sided with an α level of .05, and analyses will be performed using the R (R Foundation for Statistical Computing) or Python (Python Software Foundation) statistical packages.

To aid interpretation of the crossover design, sequence, period, and potential carryover effects will be explicitly examined. Sequence effects (AB vs BA) will assess whether the order of exposure to FibroX influences outcomes. Period effects will evaluate whether outcomes differ between the first and second study periods, independent of the intervention, which may reflect learning or temporal effects. Potential carryover effects will be explored by assessing interaction terms between intervention and study period and by comparing outcomes across sequences; a significant difference by sequence or interaction with period would suggest residual carryover. If meaningful carryover effects are detected, sensitivity analyses restricted to first-period data will be performed.

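### The two carryover checks are one weak between-clinician contrast, confounded with case set as the article reads, and it alone decides whether the first-period analysis is run

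*Protocol article*

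**What the plan says.** Clinicians are randomized 1:1 to FibroX then usual care (AB) or the reverse (BA), with a 1-week washout (Randomization; Trial Design and Oversight). On cases, Trial Design and Oversight states: "Distinct, nonoverlapping simulation case sets will be used in each study period". The stated purpose is that no clinician sees the same case twice. How sets are assigned to clinicians is not described.

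The mixed logistic model in Statistical Analysis has a random clinician effect and "study condition, study period, and sequence assignment as fixed effects", with adjustment for case covariates such as age, BMI and HbA1c. It has no case or case-set term.

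The same section says that a period effect may reflect learning or time. For carryover it states: "Potential carryover effects will be explored by assessing interaction terms between intervention and study period and by comparing outcomes across sequences", and takes significance on either as suggesting carryover. The consequence is: "If meaningful carryover effects are detected, sensitivity analyses restricted to first-period data will be performed".

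Sample Size gives the planning figures: "At least 36 health care providers (32 cases/health care provider) yield 1150 to 1280 paired decisions", with "accuracy 0.60 usual care vs 0.75 FibroX".

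**The concern.** An AB/BA design has four cell means. An intercept, condition, period and sequence describe all four, which leaves nothing for a further condition-by-period term to measure. Two listed checks that are one check give false reassurance when they agree, as they must.

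If all clinicians read one set in period 1 and the other in period 2, the period term also carries set difficulty, and the sequence contrast also carries any difference between sets in how much FibroX helps.

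The contrast compares clinicians with clinicians, so it lacks the within-clinician precision that motivates the crossover. Yet it decides whether the one analysis free of carryover is run. Carryover is plausible here, because the tool displays which variables drive risk and a clinician may retain that. If it improves later unaided decisions, it pulls the estimated effect toward zero. Those estimates feed the progression decision and the sizing of a definitive trial (Outcomes).

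**Working it through.** **1. The plan's own figures.** 36 × 32 = 1,152 and 40 × 32 = 1,280, which matches the stated range. Power for 0.60 vs 0.75 by the McNemar normal approximation, assuming independent responses: discordance ψ = 0.60 × 0.25 + 0.40 × 0.75 = 0.45 and d = 0.15. Pairs for 80% power = (1.96√0.45 + 0.842√(0.45 − 0.0225))² / 0.0225 = 155. So 1,152 pairs tolerate a design effect of 1,152/155 = 7.4, an ICC of (7.4 − 1)/31 = 0.21. The claim "McNemar test provides >80% power to detect a 15-point improvement at α=.05" is reproduced under these assumptions. The article gives neither the ICC nor the size of its design effect. It can also be read as 16 or 32 cases per period, so both are run below.

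**2. Aliasing.** Code condition A = +1 and B = −1, period 1 = +1 and period 2 = −1, sequence AB = +1 and BA = −1.

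| Cell | Condition | Period | Sequence | Condition × period |
|---|---|---|---|---|
| AB, period 1 | +1 | +1 | +1 | +1 |
| AB, period 2 | −1 | −1 | +1 | +1 |
| BA, period 1 | −1 | +1 | −1 | −1 |
| BA, period 2 | +1 | −1 | −1 | −1 |

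The last two columns are identical. Intercept, condition, period and sequence have rank 4; adding condition × period leaves rank 4. A case-set column tied to period equals the period column, and the rank again stays at 4.

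**3. What the contrast can and cannot distinguish.** Expected accuracies, on the risk scale:

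| Scenario | AB p1 | AB p2 | BA p1 | BA p2 | Crossover estimate | AB mean − BA mean | First-period estimate |
|---|---|---|---|---|---|---|---|
| 10-point carryover into AB period 2 | 0.75 | 0.70 | 0.60 | 0.75 | (0.05 + 0.15)/2 = 0.10 | 0.725 − 0.675 = 0.05 | 0.15 |
| No carryover; FibroX benefit 10 points smaller on set 2 | 0.75 | 0.60 | 0.60 | 0.65 | (0.15 + 0.05)/2 = 0.10 | 0.675 − 0.625 = 0.05 | 0.15 |
| No carryover; set 2 easier by 10 points for everyone | 0.75 | 0.70 | 0.60 | 0.85 | (0.05 + 0.25)/2 = 0.15 | 0.725 − 0.725 = 0 | 0.15 |

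The first two rows agree on all three summaries. In the first, 0.10 is biased and 0.15 is right; in the second, 0.10 is the correct average over the sets and 0.15 applies to set 1 only. The third row shows that a common difference in difficulty neither biases the effect nor produces a carryover signal.

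**4. Power of the contrast.** A carryover λ appears as λ/2 in the difference of sequence means. With 18 clinicians per sequence, m cases per period, clinician SD s and within-clinician variance per decision v = (0.60 × 0.40 + 0.75 × 0.25)/2 = 0.21375:

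SE = √[(2/18)(s² + v/(2m))]; power = Φ(λ/(2 SE) − 1.96) + Φ(−λ/(2 SE) − 1.96).

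| m | s | SE | Power, λ = 0.10 | Power, λ = 0.15 |
|---|---|---|---|---|
| 16 | 0.05 | 0.0319 | 0.35 | 0.65 |
| 16 | 0.10 | 0.0430 | 0.21 | 0.41 |
| 32 | 0.05 | 0.0255 | 0.50 | 0.84 |
| 32 | 0.10 | 0.0385 | 0.25 | 0.50 |

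λ and s are assumptions. These SDs correspond to ICCs of roughly s²/v: 0.0025/0.21375 = 0.01 and 0.01/0.21375 = 0.05. At ICC 0.10, power for λ = 0.10 is 0.15–0.16; at ICC 0.20 it is 0.11.

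**5. What rotation changes.** With both sets used in both periods within each sequence, intercept, condition, period, sequence and case set have rank 5, and adding condition × case set gives rank 6. Condition × period is still the sequence column (rank stays 5).

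**The case against.** Several stronger readings are tempting, and the article does not support them.

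- *Case set is certainly tied to period.* The design sentence guarantees that no clinician repeats a case; it does not expressly exclude rotation, and a condensed article may omit such detail. The tie is the plain reading, no more.
- *Unequal case sets bias the FibroX effect.* They do not. Each set is read under both conditions, 1:1, and period is in the model. Only a different FibroX benefit by set causes trouble.
- *The plan runs a two-stage test that inflates type I error.* The first-period analysis is labelled a sensitivity analysis. Simulated inflation to 0.075–0.082 would arise only if it replaced the crossover result.
- *The model will be rank-deficient.* The listed model has main effects only; nothing says that both carryover terms enter one fit.
- *Carryover will usually be missed.* That depends on the inputs: with 32 cases per period and clinician SD 0.05, power reaches 0.84 for a 15-point carryover. Case-level feedback is withheld in both periods, and the trigger word is meaningful, which need not be a p-value alone, although the sentence before it speaks of significance.

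It is also fair that diagnostic performance is a secondary outcome, that progression asks only for improved or comparable performance, and that weak carryover tests are common to all two-period crossovers.

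None of this makes the two checks distinct, or gives a reason to make the first-period estimate conditional on the contrast.

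**Conclusion.** The point holds in limited form. The aliasing is exact and needs no assumption. The confounding with case set holds on the plain reading of the design section: a period effect cannot be read as learning, and a carryover signal cannot be told from a condition-by-case-set interaction. Adjusting for age, BMI and HbA1c addresses this only in part.

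The size of the power problem rests on assumed inputs. A 10-point carryover that cuts the 15-point effect to 10 is detected about 21–35% of the time with 16 cases per period and 25–50% with 32, for clinician SD 0.05–0.10. Power is higher with less clinician variation or larger carryover, and lower with more variation. The harm is a missed or misread warning about a secondary estimate that informs the next trial, not an invalid main comparison.

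**What to change.** 1. Rotate the two case sets over periods within each sequence: randomize to four arms, AB or BA crossed with set 1 or set 2 first. If rotation is already planned, say so in Trial Design and Oversight.
2. Add case set as a fixed effect. Case set and condition × case set then become estimable, and the first-period estimate averages over both sets.
3. Describe the carryover check as a single sequence contrast, drop condition × period as a separate check, and name case set among the possible causes of a period effect if rotation is not adopted.
4. Report the first-period estimate unconditionally, as a sensitivity analysis beside the crossover estimate.

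Rotation removes case-set confounding only; the carryover contrast stays single and gains no power, which is why step 4 is needed.

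The cost is a revised randomization schedule, one model term and a few sentences. Recruitment had not begun and the case library was still being validated at submission, so this is feasible now and not after launch. A small downside is that both sets circulate in both periods, so clinicians should be asked not to discuss cases.

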### Monitoring, Harms, and Auditing

Given simulated, minimal-risk procedures, no independent monitoring board will be convened. The research coordinator will track enrollment, completion, protocol adherence, and technical issues weekly. Anticipated risks are limited to time burden and performance discomfort; scheduling flexibility, planned breaks, and aggregated reporting mitigate these risks.

### Ethical Considerations

Institutional review board (IRB) approval has been obtained from the Yale University IRB (HIC 2000027433). Electronic informed consent will be obtained from all health care providers prior to participation. In addition, protocol amendments will be documented, versioned, and communicated to the IRB and trial registry before implementation when required. Participants will not receive financial compensation for participation. All data will be handled in accordance with institutional privacy and confidentiality policies, with secure storage on encrypted servers and restricted access to authorized study personnel only.

All data reside on Health Insurance Portability and Accountability Act (HIPAA)–compliant, access‑controlled servers with encryption at rest and in transit, role‑based permissions, and audit trails. A master linkage file is stored separately. Only authorized staff have access to identifiable enrollment information; analysis datasets are deidentified. Data retention follows institutional policy and sponsor requirements.

### Study Status and Timeline

This manuscript describes a prospective study protocol. At the time of submission, participant recruitment and data collection had not yet commenced. The trial was registered with ClinicalTrials.gov (NCT07305324). Additional study status details and anticipated milestones are summarized in the Results section.

### Reporting and Dissemination

This protocol has been developed in accordance with the SPIRIT (Standard Protocol Items: Recommendations for Interventional Trials) 2025 statement and the SPIRIT-AI extension for clinical trial protocols involving AI intervention [24,25]. The study schedule is presented in Table 1, in accordance with the SPIRIT framework. The completed SPIRIT checklist is provided as Multimedia Appendix 1. Upon completion of the study, findings will be submitted for presentation at a relevant professional society meeting and for publication in a peer-reviewed journal. The final results manuscript will adhere to CONSORT (Consolidated Standards of Reporting Trials) guidelines [26,27]. In addition, lay summaries will be prepared for participating sites and disseminated through professional networks to facilitate knowledge translation and support future implementation. Deidentified datasets and analysis code will be made available upon reasonable request following publication and appropriate data‑sharing agreements. Findings will be disseminated via conferences, a peer‑reviewed manuscript, and lay summaries for participating sites.

**Table 1 table1:** Study schedule of enrollment, interventions, and outcome assessments (SPIRIT [Standard Protocol Items: Recommendations for Interventional Trials] framework).

Domain and procedure				Enrollment		Allocation		Intervention period 1		Washout		Intervention period 2		Closeout
				T–2 weeks to T0^a^		T0		T1^b^ (1-2 wk)		T2^c^ (1 wk)		T3^d^ (1-2 wk)		T4^e^
**Enrollment**														
	Eligibility screen and recruitment		✓											
	Informed consent		✓											
	Orientation and technical competency check		✓											
**Allocation**														
	Randomization to sequence (AB^f^ or BA^g^)				✓									
**Intervention**														
	FibroX-enabled care (condition A)						✓^h^				✓^i^			
	Usual care (condition B)						✓^i^				✓^h^			
**Assessments**														
	**Feasibility outcomes**													
		Decision time (workflow efficiency)					✓				✓			
		Usability (SUS^j^ score)					✓				✓			
		Trust in AI^k^ (AI trust scale)					✓				✓			
		Cognitive workload (NASA-TLX^l^)					✓				✓			
	**Effectiveness outcome**													
		Diagnostic accuracy (sensitivity, specificity, and AUROC^m^)					✓				✓			
	**Secondary outcomes**													
		Referral rates, confidence, and override rates					✓				✓			
		Qualitative debrief interview (barriers and facilitators)											✓	
		Final data verification and feedback											✓	

^a^T0: baseline or randomization.

^b^T1: first intervention period.

^c^T2: washout.

^d^T3: second intervention period.

^e^T4: study closeout.

^f^Sequence AB: FibroX-enabled care in period 1 followed by usual care in period 2.

^g^Sequence BA: usual care in period 1 followed by FibroX-enabled care in period 2.

^h^In Sequence AB.

^i^In Sequence BA.

^j^SUS: System Usability Scale.

^k^AI: artificial intelligence.

^l^NASA-TLX: National Aeronautics and Space Administration Task Load Index.

^m^AUROC: area under the receiver operating characteristic curve.

## Results

IRB approval has been obtained. At the time of manuscript submission, participant recruitment had not yet commenced. Preparatory activities, including platform finalization, simulation interface testing, and case library validation, were ongoing in advance of the anticipated study start date of June 15, 2026. Primary completion is anticipated on May 15, 2027, with overall study completion anticipated on June 15, 2027.

## Discussion

### Anticipated Findings

This pilot trial addresses a critical gap in diabetes care: the underdiagnosis of MASLD-associated advanced liver fibrosis despite its strong association with adverse hepatic and cardiovascular outcomes. Current noninvasive tools underperform in T2D populations, and workflow barriers further limit guideline-concordant screening. Because FibroX is not currently used in routine clinical practice, this study evaluates its feasibility, usability, and preliminary diagnostic effectiveness within simulated clinical workflows before progression to real-world implementation. A health care provider–level randomized crossover simulation design was chosen to ensure each clinician serves as their own control, improving internal validity and reducing between–health care provider variability while enabling rigorous paired analyses. Simulation with deidentified or synthetic cases minimizes risk and isolates decision performance from external clinical confounders while preserving the EHR-like context needed to assess workflow integration. This approach allows preliminary evaluation of feasibility, usability, and diagnostic performance in a controlled setting before progression to real-world clinical testing. In addition to improving risk estimation, the inclusion of SHAP-based explanations is designed to make model outputs more interpretable and actionable, potentially supporting more consistent and guideline-aligned decision-making compared with usual care.

### Comparison to Prior Work

Prior studies of machine learning in MASLD and fibrosis risk stratification have largely focused on retrospective model development and diagnostic performance, with comparatively less attention to clinician-facing usability, workflow integration, and implementation [19,21,28]. Explainable approaches such as SHAP have been proposed to improve interpretability, but prospective evaluation of how such tools influence clinical decision-making remains limited [29,30]. In this context, this pilot study extends prior work by moving beyond retrospective validation to assess FibroX as a clinician-facing decision support tool within a simulated workflow environment.

### Strengths and Limitations

This study has several strengths, including its randomized crossover design, within-clinician comparison, standardized simulated cases, and explicit assessment of feasibility, usability, and preliminary diagnostic performance. At the same time, it has limitations inherent to simulation-based designs, including the absence of real-world workflow pressures, competing clinical demands, and direct patient interaction. These features make the study well-suited for an initial pilot evaluation, but clinician behavior in simulated scenarios may not fully reflect decision-making in routine practice. Future research will therefore need to validate these findings in real clinical settings, assess longer-term implementation and outcomes, and examine scalability across diverse health systems, including resource-limited environments where MASLD burden is high.

### Future Work

If FibroX demonstrates acceptable feasibility, usability, and preliminary diagnostic performance in this pilot setting, the next step will be a larger pragmatic study in real-world clinical practice to evaluate workflow impact, referral patterns, and diagnostic effectiveness under routine care conditions. Such work should also assess generalizability across diverse practice settings, including community clinics and resource-limited environments, examine longer-term implementation outcomes, and further evaluate whether SHAP-based explanations improve interpretability and clinician trust in routine care.

### Conclusions

In conclusion, this pilot will provide early evidence on the feasibility, usability, and preliminary clinical utility of FibroX within simulated diabetes care workflows. The findings will help determine whether further real-world evaluation of this explainable AI approach is warranted for MASLD risk stratification in people with T2D.

## Appendix

Multimedia Appendix 1 SPIRIT checklist.

## Abbreviations

AI: artificial intelligence
ALT: alanine aminotransferase
AST: aspartate aminotransferase
CONSORT: Consolidated Standards of Reporting Trials
EHR: electronic health record
FIB-4: Fibrosis-4 Index
HbA_1c_: hemoglobin A_1c_
HIPAA: Health Insurance Portability and Accountability Act
IRB: institutional review board
MASLD: metabolic dysfunction–associated steatotic liver disease
NASA-TLX: National Aeronautics and Space Administration Task Load Index
SHAP: Shapley Additive Explanations
SPIRIT: Standard Protocol Items: Recommendations for Interventional Trials
SUS: System Usability Scale
T2D: type 2 diabetes
VCTE: Vibration-Controlled Transient Elastography
